### Interim analyses {21b}

No interim analyses are planned and no interim data will be shared.

### Methods for additional analyses (e.g., subgroup analyses) {20b}

For exploratory outcome variables, symptoms of anxiety will be assessed by GEE, and differences in infant sleep measures, measured only at postpartum, will be assessed using ANOVA.

### Methods in analysis to handle protocol non-adherence and any statistical methods to handle missing data {20c}

Analyses will be conducted on an intent-to-treat (ITT) basis, including data for each participant who was randomized, regardless of their adherence to the intervention or whether they withdraw from the study. Analyses including only patients completing the treatment will also be conducted.

### Plans to give access to the full protocol, participant level-data, and statistical code {31c}

As the primary investigator, [name] will remain the custodian of the data collected during the trial. Data will not be released to any third party (including the funder) before trial completion and will be analyzed independently by the study team. Recognizing the importance of sharing results, data will be shared in accordance with the International Committee of Medical Journal Editors’ guidelines, which state that authors share with others the deidentified individual patient data underlying results presented in the trial reports (including tables, figures, and appendices or supplementary material) no later than 6 months after publication. Data will be made available upon request to the primary investigator.

### Composition of the data monitoring committee, its role, and reporting structure {21a}

The trial will be monitored by the study investigators. The primary investigator will meet bi-weekly with the research coordinator to review recruitment, randomization, and assessment completion. A formal data monitoring committee is not needed for the current trial given its relatively small sample size (62 participants), short duration (5 weeks of psychological intervention), and known minimal risks (no anticipated discomforts or inconvenience to participants, some may experience mild fatigue).

### Adverse event reporting and harms {22}

No adverse events were reported in our pilot studies, and to our knowledge, no known risks to pregnant women are associated with CBT-I. To ensure participant safety, we have a treatment algorithm in place to triage participants reporting adverse events to appropriate acute or long-term treatment. The primary investigator will check in weekly with the research coordinator and therapists to ensure that the study participants’ concerns and questions are responded to appropriately.

The University of Calgary’s standard procedures will be followed for reporting adverse events and protocol violations/deviations to the Conjoint Health Research Ethics Board and privacy breaches to the Access and Privacy Coordinator.

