### Intervention description {11a}

The Sleeping for Two adaptation for CBT-I in pregnancy consists of five weekly 60-minute individual therapy sessions of CBT-I. Participants are asked to use a daily sleep diary for self-monitoring and receive a manual containing readings summarizing the material being taught in-session. The manual was adapted from a treatment protocol previously validated for oncology patients with comorbid insomnia [87]. In adapting the CBT-I protocol for use with pregnant women, we followed steps outlined in the ORBIT Model [74, 75] for developing behavioural therapies to treat or prevent chronic diseases and enhance health-promoting behaviours (e.g., sleep): Phase I (i.e., defined the question), Phase IIa (i.e., created a fixed treatment package; see Appendix A for session structure), Phase IIb (i.e., pilot tested the intervention), and Phase III (i.e., a randomized controlled trial; RCT). This manuscript represents Phase III.

During this five-session intervention, patients are familiarized with the self-management approach for insomnia (e.g., active vs. passive coping strategies). First, patients are oriented to CBT-I (e.g., use of daily sleep diaries) and set individualized treatment goals (Session 1). The remaining sessions consist of weekly review of sleep diaries, psychoeducation about sleep and sleep consolidation (Session 2), stimulus control (Session 3), cognitive strategies to examine attitudes and beliefs about sleep (Session 4), and problem-solving to cope with sleep disturbances and relapse prevention (Session 5). In the final session, participants are also provided information on infant sleep and the importance of mutual regulation, which was adapted from evidenced-based behavioural-education programs [88] and consultation with infant sleep experts. A licensed clinical

psychologist with extensive training in CBT-I will supervise the administration of the intervention ([name]).

The control group will receive regular obstetric care provided according to the needs and current regime of the patient. The amount of contact with health care professionals outside of the study will be recorded, coded, and reported, as well as any treatment for insomnia (e.g., medication use, searching the internet for techniques to improve sleep) that the patient engages in. After study completion, TAU participants will be offered the CBT-I intervention, which has been successfully delivered in the postpartum [86].

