**Fig. 1 Fig1:**
[figure not shown]
SPIRIT schedule of enrolment, intervention, and assessments

Week 1 (T1): Eligible participants will meet with a member of the research team at the laboratory or via an online assessment hosted using the Jane App, who will explain the study protocols and obtain consent (either written or via Qualtrics). Participants will be asked to complete the series of structured clinical interviews, self-report questionnaires via Qualtrics, and then are provided with an actigraphy device and a link to an online daily sleep diary to complete for a period of 7 consecutive days.

Week 2: Participants will be randomly allocated to CBT-I or TAU.

Weeks 2 to 6: If randomized to the treatment group, participants will be invited to attend 5 sessions of CBT-I in person or via telehealth. Participants in the TAU group will receive regular obstetric care provided according to the needs and current regime of the patient.

Week 7 (T2): After 7 weeks, all the participants will be invited to complete the same set of questionnaires from the baseline assessment. Additionally, participants will be sent an Actiwatch and a link to an online daily sleep diary to complete for a period of 7 days.

Six months postpartum (T3): At 6 months postpartum, all participants will be invited to a web-link with the same set of questionnaires from the previous points of assessment, as well as one additional questionnaire assessing infant sleep quality. Participants will also be sent an actiwatch and a link to an online daily sleep diary to complete for a period of 7 days.

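### Adverse events are captured by participant report, with a weekly therapist channel in the CBT-I arm only, so reported event counts should not be compared by arm without common questions

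*Protocol article*

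**What the plan says.** Three parts of the protocol article bear on this point.

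- **Adverse event reporting and harms {22}.** Handling begins when a woman reports something: "we have a treatment algorithm in place to triage participants reporting adverse events to appropriate acute or long-term treatment". The routine check is described as follows: "The primary investigator will check in weekly with the research coordinator and therapists", so that whatever participants raise gets an appropriate response. Onward reporting is by institutional rule: the university's "standard procedures will be followed for reporting adverse events and protocol violations/deviations to the Conjoint Health Research Ethics Board".
- **Intervention description {11a} and Participant timeline {13}.** The treatment "consists of five weekly 60-minute individual therapy sessions of CBT-I", delivered in weeks 2 to 6. For the same weeks the timeline says of the control arm: "Participants in the TAU group will receive regular obstetric care provided according to the needs and current regime of the patient". Under Provisions for post-trial care {30}, TAU women are offered CBT-I only after the follow-up visit, so they have no study therapist during the comparison.
- **Composition of the data monitoring committee {21a}.** The expected risk is given as "no anticipated discomforts or inconvenience to participants, some may experience mild fatigue".

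The Outcomes {12} section and the measures under Plans for assessment and collection of outcomes {18a} contain no adverse-event question for either arm, and they do not list fatigue as a harm to be collected.

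**The concern.** When events are recorded only if a participant mentions them, the number recorded depends on how often she has an occasion to mention them. A CBT-I woman has a weekly hour with a study therapist, who is then asked about her by the investigator. A TAU woman with the same complaint has no scheduled study session until T2 and would have to raise it on her own initiative. Two arms with the same true event rate could then show different recorded counts.

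What is at stake is how a table of reported events by arm would be read. An excess under CBT-I could be an artefact of contact, and similar counts could hide a true difference in the other direction. The article foresees health-system uptake if efficacy is shown (Dissemination plans {31a}), so readers will want harms data that they can interpret.

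**Working it through.** The article states no adverse-event rate, threshold or comparison, so there is no figure to reproduce. The check is a count of scheduled sessions, followed by an illustration of what unequal detection would do.

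**Step 1. Scheduled study sessions by arm**

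| Period | CBT-I | TAU | Source |
|---|---|---|---|
| Between T1 and T2 (weeks 2 to 6) | 5 | 0 | Intervention description {11a}; Participant timeline {13} |
| Assessments T1, T2, T3 | 3 | 3 | Participant timeline {13} |
| Total | 5 + 3 = 8 | 0 + 3 = 3 | |

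This counts sessions and assessments, not every contact. Booking calls by research assistants (Plans to promote participant retention {18b}) are described without distinction by arm and are not included.

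**Step 2. Channels by arm**

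| Channel | CBT-I | TAU |
|---|---|---|
| Participant's own report, then triage | yes | yes |
| Research coordinator in the weekly check-in | yes | yes |
| Therapist in the weekly check-in | yes | no |
| Adverse-event question at T2 or T3 | none described | none described |

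The third row is the imbalance. The fourth row shows that nothing described offsets it.

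**Step 3. What unequal detection would do (illustration only)**

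Let n = 31 per arm (Sequence generation {16a}), p = true event rate (the same in both arms), and d = probability that an event is recorded. Expected recorded events = n × p × d. With equal p, the apparent rate ratio is d(CBT-I) / d(TAU), whatever p is. The values of p and d below are assumptions; none comes from the document.

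With p = 0.20 and d(CBT-I) = 0.9, CBT-I records 31 × 0.20 × 0.9 = 5.6 events.

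| d(TAU) | TAU recorded | Apparent ratio |
|---|---|---|
| 0.9 | 31 × 0.20 × 0.9 = 5.6 | 0.9 / 0.9 = 1.00 |
| 0.7 | 31 × 0.20 × 0.7 = 4.3 | 0.9 / 0.7 = 1.29 |
| 0.5 | 31 × 0.20 × 0.5 = 3.1 | 0.9 / 0.5 = 1.80 |
| 0.3 | 31 × 0.20 × 0.3 = 1.9 | 0.9 / 0.3 = 3.00 |

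The table shows the direction of the artefact and that equal detection removes it. It does not estimate the artefact in this trial, because each ratio is simply the quotient of two assumed probabilities.

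**Step 4. What is collected alike in both arms**

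Insomnia severity, sleep quality, diary and actigraphy measures, and depressive symptoms follow one schedule for all participants (Participant timeline {13}). Staff collecting these data and psychologists supervising the follow-up diagnostic interviews are blinded to group (Who will be blinded {17a}). Gestational length, delivery type and birth weight come from health-record linkage (Secondary outcomes, under {18a}). The imbalance in Step 2 does not touch any of these.

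**The case against.** The case on the other side is substantial, and much of it stands.

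- **Therapists are not the only channel.** A reader might infer that concerns reach the investigator only through therapists. The same sentence names the research coordinator, who serves both arms. This stands. However, no coordinator session with TAU women is scheduled in weeks 2 to 6, so the shared channel does not cancel the extra one.
- **Worsening in TAU women is visible.** A reader might infer that deterioration in untreated women would be missed. It would not: sleep and mood are what the trial measures most fully, on the same plan in both arms. The intervention section also says that outside health-care contact and insomnia treatment will be recorded, in its paragraph on the control group. This stands, and it confines the point to reported adverse events.
- **No comparison of adverse events is planned.** The statistical sections list none, and the stated purpose of the weekly check-in is to respond to participants. This stands too: no planned analysis is biased. What remains is the risk that event counts are tabulated by arm and read as a comparison.
- **The article is condensed.** Adverse-event forms may sit in the full protocol, the triage algorithm or the university procedures. That is possible, and a missing form alone would not be a finding. The point rests on the route that the article does state, which is unequal by arm. The university procedures are cited for reporting to the ethics board, which is a different matter from finding events.
- **The risk wording is a quibble.** The phrase that denies discomforts and then mentions mild fatigue can be read as a rule with a minor exception. It changes no result and is not pressed here, except that the named fatigue is an obvious item to ask about.

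**Conclusion.** The concern holds in a limited form. As described, adverse events are captured when participants report them, and one of the two sources in the weekly check-in exists only for CBT-I women: 5 scheduled sessions against 0 for TAU in weeks 2 to 6. Counts of reported adverse events, chiefly from those weeks, are open to unequal ascertainment. The likely direction is that CBT-I would look more harmful. The size is unknown, and no inflation factor can be derived from the document.

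The conclusion assumes that more scheduled contact leads to more recorded events, and that no arm-neutral adverse-event question exists in documents not shown. If such a question is already asked in both arms at the same times, the collection problem falls away and only the separate listing of therapist-sourced events remains to be stated.

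The broader reading, that harms in this trial cannot be compared between arms at all, is not supported. Insomnia, sleep quality, depression, psychiatric diagnoses and birth outcomes are collected alike and can be compared.

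**What to change.** 1. Add one short adverse-event item set, identical in wording and recall period for both arms, to the T2 and T3 Qualtrics questionnaires. Include the fatigue named in the data monitoring section. Sleep and mood worsening need no new items, because existing scales cover them.
2. Base any adverse-event table by arm on those items and on the outcomes already collected alike in both arms.
3. List events that surface only through therapists separately, label them as such, and do not compare them between arms.

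**Timing.** Trial status reports that recruitment closed on October 21, 2020, with the last visit expected in November 2021. T2 falls in week 7, so it may already be past for most or all women. In that case, add the items to the assessments that remain, in both arms. Items first asked at 6 months postpartum recover weeks 2 to 6 only through long recall, so reports from those weeks should then be described without comparison. The reporting rules in steps 2 and 3 can be adopted whatever the stage of follow-up.

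**Cost.** The questionnaire becomes slightly longer, and more events will be counted than under spontaneous reporting. No new visit or staff is needed.

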### Frequency and plans for auditing trial conduct {23}

There are no plans for independent auditing of trial conduct. The Conjoint Health Research Ethics Board may request an audit.

### Plans for communicating important protocol amendments to relevant parties (e.g., trial participants, ethical committees) {25}

Amendments to the protocol will be submitted and reviewed for approval by the Conjoint Health Research Ethics Board at the University of Calgary. If the amendment requires the revised information to be provided to participants currently enrolled in the study trial, this is communicated through a consent addendum. For example, COVID-19 was declared a global pandemic in March 2020, part way through the trial; therefore, the protocol was modified to provide the intervention via telehealth through a secure virtual platform, following local regulations; and participants received a telehealth consent form addendum.

### Dissemination plans {31a}

Using a multifaceted approach, research findings will be disseminated to academic and nonacademic audiences. To communicate research findings to the public and knowledge users, we will share key findings through our study and lab website and through social media channels. Second, we will work with Media Relations at the Alberta Children’s Research Institute (ACHRI) and the University of Calgary to disseminate findings through local and national media outlets. We will use existing community contacts to host presentations that share findings with specific perinatal and parenting groups and educators. We will disseminate our research with academic and professional audiences via presentations at conferences and publication of findings in high impact journals, consistent with the Tri-Agency Open Access Policy. In addition, if trial findings substantiate the efficacy of CBT-I in pregnancy, we will coordinate with our applied health research partners (e.g., Strategic Clinical Networks) to explore opportunities for health system integration through implementation and scale-up funding.

## Discussion

CBT-I delivered in pregnancy has the potential to reduce symptoms of insomnia and depression and could lead to reduced risk of preterm birth, all of which can minimize risk of negative maternal and child health and developmental consequences in the short (e.g., infant death) and long terms (e.g., developmental delays). This RCT builds on the successful open pilot trial conducted by our team and will provide further evaluation of a novel evidence-based treatment for pregnancy-related insomnia, which can be widely disseminated and used to treat individuals that are most in need of intervention. Moreover, the challenges presented by the COVID-19 pandemic and ensuing physical distancing measures led to modifications in the protocol to ensure treatment could continue to be provided, via telehealth. This will be the first study to investigate the delivery of CBT-I via telehealth (videoconferencing) during pregnancy. Findings will enhance understanding of pregnancy-related sleep problems, as well as means by which to improve the health and sleep of both mothers and their children.

## Trial status

The trial protocol was last updated on April 15, 2020 (Version 4). Recruitment began on July 24, 2019, and was anticipated to finish in January 2021 (with estimated study completion in January 2022 for collection of all primary outcomes). However, there was a significant influx of interest in participating in the trial after COVID-19 was declared a global pandemic in March 2020, when the protocol was modified to offer the intervention via telehealth due to social distancing guidelines, leading to recruitment finishing earlier than anticipated on October 21, 2020. Given the ensuing increased study operation demands, we were not able to submit the protocol sooner. The last patient visit is now estimated to be completed in November 2021.

## Appendix

### Structure of cognitive-behavioral therapy for pregnant women with insomnia

Session1: Introduction

1. Discuss the overview of the CBT-I program and the basic principles of how to cope with sleep problems.
2. Help participants set realistic goals for what they can get out of the program.
3. Discuss the importance of self-monitoring.
4. Encourage participants to practice using the Daily Sleep Diary.

Session 2: Sleep basics and sleep consolidation

1. Psychoeducation about the basic biology of sleep and to become familiar with terms such as sleep efficiency, sleep stages, and slow-wave sleep.
2. Recognize and understand the controllable and uncontrollable factors that affect sleep, such as alterations of hormonal changes that can affect sleep quality and quantity during pregnancy
3. Present the rationale behind the behavioral strategies for managing sleep disturbances.
4. Discuss about the importance of mastering the technique of sleep consolidation.

Session 3: Stimulus control

1. Review progress using sleep consolidation procedures and help adjust the sleep window.
2. Learn stimulus control procedures as a means of re-establishing a positive association between bed and sleeping.
3. Talk about steps to take control of sleep problems.

Session 4: Cognitive therapy

1. Discuss self-defeating thoughts, negative feelings, and poor sleep behaviors.
2. Review biased ways of thinking about sleep, signs that self-talk may be negative and self-defeating and the categories of negative self-talk.
3. Examine attitudes and beliefs about sleep.
4. Discuss the general techniques for managing stress.
5. Identify and challenge participants’ negative self-talk about their sleep.

Session 5: Problem solving and relapse prevention

1. Talk about problem solving to cope with sleep disturbances (S.O.L.V.E. Technique).
2. Emphasize the importance of maintaining treatment gains and continuing to work towards better sleep.
3. Discuss about effective ways to cope with relapse, especially in the postpartum period.
4. Discuss infant sleep and how to best establish health habits for infants in the postpartum period.

## Abbreviations

BISQ: Brief Infant Sleep Questionnaire
CBT: Cognitive behavioral therapy
COVID-19: Coronavirus disease 2019
DIAMOND: Diagnostic Interview for Anxiety, Mood, and OCD and Related Neuropsychiatric Disorders
DSM: Diagnostic and Statistical Manual of Mental Disorders
EPDS: Edinburgh Postnatal Depression Scale
GEE: Generalized estimated equations
ISI: Insomnia Severity Index
ITT: Intent-to-treat
ORBIT: Obesity Related Behavioral Intervention Trials
PPD: Postpartum depression
PSA: Pregnancy Specific Anxiety
PSQI: Pittsburgh Sleep Quality Index
RCT: Randomized controlled trial
RLS: Restless legs syndrome
SCISD: Structured Clinical Interview for DSM-5 Sleep Disorders
SDB: Sleep-disordered breathing
STAI: Strait Trait Anxiety Inventory
TAU: Treatment as usual
